### Estimating the cost effectiveness of the intervention on health service outcomes

A cost–benefit analysis (CBA) of the intervention will be undertaken. The cost calculation will include both direct and indirect costs to both NHS and care homes delivering the intervention. Benefits are calculated as the change in NHS costs incurred following the intervention. This will be estimated by valuing the reduction in hospital stays and hospital days as a result of the intervention. These will be measured using hospital day rates and ambulance costs. Where possible, data will also be collected on additional costs, such as hospital transfers via taxi and primary care use.

The CBA will be conducted from the perspective of the NHS and Personal Social Services. The costs of the intervention will be compared with the changes in health service costs from reduced hospitalisation. The costs and benefits will be calculated taking account of (1) uncertainty in the estimate of the treatment effect; (2) projected costs over a 5-year period; and (3) spatial variation in cost across jurisdictions. Wherever possible the analytical specification will follow that of the National Institute of Health and Care Excellence (NICE) Reference Case.^44^ While there are also likely to be individual and broader societal benefits arising from the intervention, these are challenging to value in financial terms and beyond the scope of this economic evaluation. They will be explored through the qualitative data collection.

The net benefits of the intervention will be modelled over a 5-year period separately for care homes in (1) England and (2) Scotland, given the estimate of cost savings per care home bed and the total number of care home beds in each jurisdiction, and applying an annual discount rate. These predictions will be modelled at the point estimate for the treatment effect, and also for the upper and lower bounds of the 95% CI around the treatment effect, to provide a range of plausible costs savings over 5 years incorporating the uncertainty in the main study.

The treatment effect will be estimated using a pre and post design. One limitation of this design is that aggregate time trends can be a confounder. Attempts have been made to mitigate this by using multiple sites across the country, and by measuring the baseline and post-treatment outcomes at the same time of year. However, national-level time trends could explain part of the differences observed and this will be reflected on when interpreting the results.

The uncertainty of the estimated treatment effect will be represented in the cost effectiveness analysis. The 95% CIs from the estimated treatment effect will be used to calculate estimated cost effectiveness ranges, that is, the cost effectiveness will be reported at (1) the lower bound of the 95% CI; (2) the point estimate of the treatment effect; and (3) the upper bound of the 95% CI. Reporting a cost effectiveness range will allow the uncertainty in the treatment estimate in the cost effectiveness figures to be captured. Some subgroup analysis is likely to be conducted, for example, to examine cases focused on independent specialist palliative care teams, and public versus private care homes.

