### Outcomes

The primary outcome is to determine *what works, for whom, in what circumstances,* for UK Needs Rounds. Secondary outcomes focus on health service use, alongside quality of death and dying, staff capability to adopt a palliative approach, and family perceptions of care. The core economic outcome is the total change in health and social care service costs that result from the intervention.

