	Costs of taxis to transfer residents to hospital	Collected from care home sites in a proforma through interviews.
Indirect costs	Wider additional costs incurred by the care home, including: Changes in their staffing Changes to facilities (ie, use of rooms), or overheads as a result of hosting the intervention.	These changes, and their associated costs, will be collected from care homes in a proforma through the interviews
Intangible costs	Inconvenience to staff, residents, family and carers as a result of the intervention.	These will not be measured directly, but will be explored in the qualitative interviews.

**Table 4 T4:** Health service cost elements

Cost type	Cost detail	Measurement of costs
Direct costs	Costs of ambulance journeys	Estimated from the 2019/20 National Tariff Payment System.^47^
	Hospital stay cost	Hospital-specific Patient Level Information and Costing System data for England^48^ and Scotland^49^ on stay costs by age and gender to estimate a day rate to use in the hospital costing.
	Primary care usage	Collected from care home sites in a proforma through interviews
Indirect costs	Wider additional costs incurred by the care home, in connection with resident hospital admissions, including staffing, travel, equipment or facilities.	These costs will be collected from care homes in a proforma through the interviews
Intangible costs	Inconvenience to residents and their family/carers arising from hospitalisation	These will not be measured directly, but will be explored in the qualitative interviews in the main study.

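### The cost–benefit analysis counts costs over the NHS and care homes but benefits over the NHS alone, which matches neither its stated perspective nor its own cost tables

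*Protocol article*

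**What the plan says.** All references are to the protocol article.

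*Estimating the cost effectiveness of the intervention on health service outcomes* sets three rules for the cost–benefit analysis:

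- Costs: "The cost calculation will include both direct and indirect costs to both NHS and care homes delivering the intervention".
- Benefits: "Benefits are calculated as the change in NHS costs incurred following the intervention". On valuing the reduced hospital use it says "These will be measured using hospital day rates and ambulance costs", and then "Where possible, data will also be collected on additional costs, such as hospital transfers via taxi and primary care use".
- Perspective: "The CBA will be conducted from the perspective of the NHS and Personal Social Services".

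*Outcomes* adds: "The core economic outcome is the total change in health and social care service costs that result from the intervention".

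*Data collection* bases the evaluation on Tables 3 and 4 and defines benefit as the pre-to-post difference in the cost of health service use. Table 3 (intervention costs) includes care home staffing changes, facilities and overheads, and also "Costs of taxis to transfer residents to hospital". Table 4 (health service costs) includes "Wider additional costs incurred by the care home, in connection with resident hospital admissions, including staffing, travel, equipment or facilities", to be gathered by proforma through the interviews.

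**The concern.** A net benefit is interpretable when both sides are counted for the same set of payers. Here care homes are inside the boundary when the intervention costs them something. They are outside it when a change in admissions alters what they spend. The stated NHS and PSS perspective fits neither side. It is narrower than the cost side, because Table 1 recruits homes with self-funded residents and some care home costs may therefore not fall on NHS or PSS budgets. It is wider than the benefit side, which leaves out PSS.

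The figure affected is the one the protocol projects over 5 years to every care home bed in England and in Scotland. The planned range around it takes the point estimate and the two 95% confidence limits of the treatment effect. That range carries sampling uncertainty only, so a mismatch in accounting scope would not show in it. Two analysts who followed different sections of the article could also report different net benefits from the same data.

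**Working it through.** **The plan's own figures.** The economic section states no monetary figure to reproduce. The quantities that drive the savings are in *Target sites and population*, and they check:

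- 52 beds × 0.173 admissions per bed = 9.0 admissions per home per 4 months, as stated.
- 52 beds × 0.02 = 1.04 fewer admissions per home per 4 months, the reduction of about one that the article calls clinically meaningful. This is a detectable change, not a predicted effect.

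**The scopes side by side.**

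| Place | NHS | PSS or social care | Care homes |
|---|---|---|---|
| Cost rule, cost-effectiveness section | yes | not named | yes, without limit by funder |
| Benefit rule, same section | yes | no | no |
| Perspective, same section | yes | yes | only what falls on NHS/PSS |
| Core economic outcome, *Outcomes* | health | social care | not named separately |
| Table 4, *Data collection* | yes | not named | yes, costs connected with admissions |

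The outlier is the benefit rule. *Outcomes* broadly agrees with the stated perspective.

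**What the mismatch does.** Let S be the fall in NHS costs, K_N the NHS intervention costs and K_H the care home intervention costs. Let H = ΔA × c, where ΔA is the number of admissions averted and c the net care home cost saved per averted admission. Let p and q be the shares of K_H and H that fall on NHS/PSS.

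- As written: S − K_N − K_H.
- NHS plus care homes on both sides: S + H − K_N − K_H. The gap from the written rule is H.
- NHS and PSS on both sides: S + qH − K_N − pK_H. The gap is qH + (1 − p)K_H.

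**Putting in what is known.** With ΔA = 1.04 per home per 4 months, H = 1.04c. Each £1 of c moves H by £1.04 per home, or by £1.04 ÷ 52 = £0.02 per bed, per 4 months. The document does not give c, p, q or K_H.

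**Sign.** If c is positive (escort, cover and travel avoided), the written rule leaves out a saving. If c is zero, H is zero. If c is negative (a resident who stays needs care that hospital would otherwise have given), the written rule leaves out a cost. In the NHS and PSS version, (1 − p)K_H is positive whenever the intervention adds care home costs that others pay, but qH can have either sign. The total is therefore undetermined.

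**Taxis.** Journeys to hospital follow from admissions. In Table 3 they count as a cost of delivering Needs Rounds. The cost-effectiveness section names them directly after the valuation of savings, together with primary care use, which is a Table 4 item. The two placements treat the same cost differently.

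**The case against.** The strongest defence is that the article does not leave the care home offset out everywhere. *Data collection* bases the evaluation on both tables. Table 4 puts care home admission costs under health service costs, and the cost-effectiveness section also says that intervention costs are set against changes in health service costs. On that reading the offset could be credited, and the narrow benefit sentence is loose drafting. This stands in part: the fault is a contradiction to be reconciled, not a uniform omission. It does not remove the point, because the sentence that defines benefits, and the one that says how they are valued, both stop at the NHS.

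A reader might infer more than the document supports:

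- That net benefit is biased against Needs Rounds. There is an argument for this: Table 4 describes the uncredited row as additional costs tied to admissions, which should fall with them, and Table 3 already charges staffing changes. But no unit cost is given. Keeping residents in the home could raise its costs, and nothing says that Table 3 would capture all of that.
- That the core economic outcome is a third, competing definition. It broadly matches the NHS and PSS perspective.
- That workshop costs in Table 3 would recur each year of the projection. Nothing says so, and separating one-off from recurring costs is detail that an article can leave to a fuller plan.

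The primary outcome of the study is qualitative and is not touched.

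**Conclusion.** The point holds as an inconsistency in stated rules. The cost and benefit sides of the net-benefit calculation cover different payers, neither side matches the declared perspective, and the benefit rule conflicts with *Outcomes* and with Table 4. The taxi row is placed inconsistently as well. The projected net benefit may therefore be biased.

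The direction and size of any bias cannot be known from the document. Against a matched NHS-plus-care-home result the gap is 1.04c per home per 4 months, if the true effect equals the detectable change of 0.02 per bed. Against a matched NHS and PSS result it also depends on how much care home cost falls outside NHS/PSS. Whether the gap is material beside the hospital savings is not shown either, since no cost is stated for any component. The case for change is that the main economic figure should have one meaning and that the correction is cheap.

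**What to change.** 1. Apply one payer scope to both sides of the primary net-benefit result. Under the stated NHS and PSS perspective, charge only those care home costs that fall on NHS or PSS budgets, and define benefit as the change in NHS and PSS costs.
2. If all care home costs are charged, for example in a secondary result, also count the change in the Table 4 care home admission costs: a cost per admission from the proforma, multiplied by the estimated change in admissions.
3. Move the taxi row from Table 3 to Table 4, so that it is handled as a cost of hospital use.
4. Give the same benefit definition in *Data collection* and in the cost-effectiveness section.

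The cost is some rewording and a little more analysis. One limit should be stated. The Table 4 care home costs come from proformas completed through interviews, the Phase 2 interviews are at 4, 8 and 12 months of implementation, and no pre-implementation collection of these costs is described. A direct pre–post comparison of them may not be possible. That is why a cost per admission is suggested, and it may have to be reported as an explicit assumption.

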### Intervention description

Needs Rounds are monthly hour-long triage meetings focused on 8–10 residents in each care home who are at risk of dying without a plan in place. A checklist^25^ is used to identify the most appropriate residents to discuss. Needs Rounds are chaired by a palliative care specialist and attended by care home staff who discuss each resident’s physiological, psychosocial and spiritual needs. This instigates a number of tailored actions, which are always personalised for the individual, including medication reviews, case conferences, anticipatory/advance care planning and referrals to relevant specialists.

Needs Rounds have a strong evidence base to support their uptake. Research in Australia demonstrated a number of positive outcomes. Needs Rounds reduced the length and number of hospitalisations,^26 27^ increased resident dying in their preferred place,^26^ with dignity, compassion and comfort,^28^ enabled staff to normalise death and dying,^29^ and improved workforce confidence.^28^

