Care homes (adopting Needs Rounds as their new standard of care). n=28–36	Located near to the specialist palliative care team Provide care to residents who have high clinical nursing/medical needs Willing to sign a memorandum of understanding with the research team, outlining resident demographics and health service use data, facilitate access to staff for interviews, and engagement in Needs Rounds A range of sizes (focusing primarily on larger care homes, following CQC data indicating lower quality in larger facilities),^46^ sole traders and large corporate provider, and with a range of funding models (NHS/social care and self-funded residents).
Residents (discussed at Needs Rounds in phase 2) Estimate of n=1500	Resident in a collaborating care home in one of the six case study locations An anticipated life-expectancy of less than 6 months At risk of dying without appropriate planning in place Experiencing inadequately managed bio-psychosocial symptoms Not engaged in any current safeguarding investigations Able to provide their own informed consent
Relatives (completing outcome measures in phase 2) n=300	The relative of a resident who was discussed in Needs Rounds Able to provide their own informed consent.
PPI evaluation n=15	Coinvestigator or a member of one of the case study sites Able to provide their own informed consent

CQC: Care Quality Commission; NHS: National Health Service

For the quantitative sample, the average size of the care homes is anticipated to be 52 beds, and the rate of emergency admission to hospital to be 0.173 per bed within the 4-month period,^37^ with an average of 9 admissions per care home. A sample of 30 care homes would allow change to be identified in the hospitalisation rate of 0.02 per bed (α=0.05, β=0.2, ΔSD=0.040). This is sufficient to detect a clinically meaningful change in the primary outcome (reduction of one hospitalisation per 4 month period in a typical care home) for the quantifiable data in phase 2.

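### The 5-year national net benefit is scaled by beds alone, although a substantial part of Needs Rounds delivery is set per home, so delivery cost is mis-scaled for homes that differ in size from the study average

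*Protocol article*

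**What the plan says.** In the protocol article, the section on estimating cost effectiveness states the quantity to be projected: "The net benefits of the intervention will be modelled over a 5-year period separately for care homes in (1) England and (2) Scotland". The inputs follow in the same sentence: "given the estimate of cost savings per care home bed and the total number of care home beds in each jurisdiction", with annual discounting. The projection is run at the point estimate of the treatment effect and at the two limits of its 95% confidence interval.

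On costs, the same section says: "The cost calculation will include both direct and indirect costs to both NHS and care homes delivering the intervention". It adds: "The costs of the intervention will be compared with the changes in health service costs from reduced hospitalisation". Among the things to be taken into account it lists "projected costs over a 5-year period", without saying whether these are per home or per bed.

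The Intervention description gives the unit of delivery: "Needs Rounds are monthly hour-long triage meetings focused on 8–10 residents in each care home". The opening of Methods and analysis asks for two or more facilitators in every home. Table 1 asks for homes of a range of sizes, "focusing primarily on larger care homes", and the sample-size paragraph anticipates 52 beds on average.

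**The concern.** Savings and delivery cost do not grow with the same quantity. The treatment effect is a rate per bed, so avoided admissions rise with beds. The meeting and the facilitators are specified once per home, whatever its size. A single per-bed figure from homes averaging 52 beds, applied to every bed in a jurisdiction, treats both sides as proportional to beds.

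The text also leaves open whether the per-bed saving is before or after delivery cost. The output is called net benefit at the start of the paragraph and cost savings at its end, while benefits are defined in that section as the change in NHS costs, with intervention cost a separate item.

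At stake is the sign and size of the projected net benefit for smaller homes, and possibly of the national total. The study aims at a scalable UK model, and this projection bears directly on roll-out. The planned range would not reveal the problem, because it varies only with the confidence interval of the treatment effect. The subgroups given as examples are team type and public versus private homes, not home size.

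**Working it through.** **The plan's own figures.** The article gives no delivery cost, saving per bed or national total, so there is no projection to reproduce. The related figures in the sample-size paragraph do reproduce: 52 × 0.173 = 9.0 admissions per home per 4 months, and 52 × 0.02 = 1.04 admissions avoided.

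**Savings scale with beds.** At the detectable effect, admissions avoided per year are 0.02 × 3 periods × beds: 3.1 at 52 beds, 1.8 at 30 and 1.2 at 20.

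**Core meeting time does not.** One hour a month is 12 hours per home-year. Per bed this is 12/52 = 0.23 h, 12/40 = 0.30 h, 12/30 = 0.40 h and 12/20 = 0.60 h.

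**Effect on delivery cost if the per-bed figure is net.** Let f be the share of delivery cost fixed per home in a 52-bed home, with the rest proportional to beds. For a home of B beds, true cost per bed relative to the study's cost per bed is

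r = f × 52/B + (1 − f),

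and bed scaling understates cost by 1 − 1/r. Both B and f are assumptions; the article gives neither.

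| B (assumed) | r, f = 1 | Understated | r, f = 0.5 | Understated |
|---|---|---|---|---|
| 40 | 1.30 | 23% | 1.15 | 13% |
| 30 | 1.73 | 42% | 1.37 | 27% |
| 20 | 2.60 | 62% | 1.80 | 44% |
| 52 | 1.00 | 0% | 1.00 | 0% |
| 70 | 0.74 | overstated by 35% | 0.87 | overstated by 15% |

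**National total.** With N homes of mean size b and a fixed cost C per home, bed scaling gives (C/52) × N × b, whereas the fixed cost is C × N. The formula for r therefore also applies to the national total, with b in place of B. The error is nil at b = 52 and reverses sign above it. The article does not give b.

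**Break-even size.** Let R be the ratio of saving to delivery cost in a 52-bed home (assumed). Break-even is where R = r, so B = 52f/(R − 1 + f). For R = 1.5 this is 52/1.5 = 34.7 beds at f = 1, and 26/1.0 = 26 beds at f = 0.5. A projection scaled by beds alone would show every home in surplus at this R.

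**If the per-bed figure is gross.** The two inputs named, saving per bed and total beds, contain no delivery cost. It would have to enter by a step the sentence does not describe.

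**The case against.** Four arguments against the point have weight.

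- A reader might infer that delivery cost is left out of the projection altogether. The article does not support that. It counts direct and indirect intervention costs, sets them against the savings, refers to projected costs over 5 years and calls the result net benefit. What is missing is the unit on which cost is scaled, and whether the per-bed saving is gross or net.
- Not all delivery cost is fixed per home. Table 3 includes extra NHS staff time and prescriptions, and the meetings trigger individual actions such as medication reviews, case conferences and referrals. The facilitators have no cost line of their own. The UK format is still to be codesigned. So f is unknown, and the f = 1 column is an upper illustration. This reduces the size but does not remove the effect. Triggered work may also follow the residents discussed more closely than beds: 8–10 residents are 15–19% of 52 beds but 40–50% of 20.
- A reader might infer that the national projection is certainly too favourable. That depends on a national size distribution the article does not give. Recruiting mainly larger homes makes it plausible and no more.
- An article condenses the full plan, and the scaling of each cost component may be set out there. This would answer a complaint about missing detail. It answers less well here, because the article states a scaling rule and that rule names one unit. Cost details are collected from the homes, so a better projection remains possible.

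**Conclusion.** The point holds in a limited form. The stated rule uses beds as its only multiplier, while a substantial part of delivery is set per home and the sample favours larger homes. If the per-bed figure is net, delivery cost is understated in homes below the study average and overstated above it. In the illustration the understatement is 13–23% at 40 beds and 27–42% at 30, for f between 0.5 and 1. If the figure is gross, the stated inputs do not carry delivery cost into the projection.

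These percentages rest on assumed home sizes and fixed shares and on the anticipated 52-bed average. They describe delivery cost, not net benefit, which cannot be computed from the article. The direction of any national error is not established. The matter affects a secondary, downstream projection, not the primary outcome or the estimate of the treatment effect, and is worth correcting because the correction is cheap and could change the projected result.

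**What to change.** State whether the saving per bed is gross or net of delivery cost. Then project, for England and Scotland separately and with the planned discounting:

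5-year net benefit = (gross saving per bed × beds) − (per-home delivery cost × number of homes) − (resident-varying delivery cost × beds or residents discussed).

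Do this by home-size band where counts are available, and report the break-even home size. The split between fixed and resident-varying cost can be drawn from the activity logs and cost proformas already planned.

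The cost is a change of wording in the economic model and one more external input, the number of homes in each jurisdiction, by size band if possible. No new study data are needed. The projection may become less favourable for small homes.
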